#### Outcomes

The NAVSaH trial’s evaluated end points include: 1) Defining the impact that taVNS has on the SAH-induced inflammatory markers in the plasma and cerebrospinal fluid (CSF), 2) Determining if taVNS following SAH reduces angiographic vasospasm 3) Determining if taVNS following SAH reduces chronic hydrocephalus.

For assessment of the impact taVNS has on inflammatory makers, blood and CSF is collected prior to the initial treatment session as a baseline, and then every three days during the patient’s inpatient hospital stay (CSF collected only when an external ventricular drain is in place). The primary inflammatory marker assessed is TNF-α, although a panel of 13 cytokines is analyzed in an exploratory fashion (IL-1β, IL-2, IL-4, IL-5, IL-6, IL-8, IL-10, IL-12, IL-13, IL-17, TNF-α, GM-CSF, and IFN-γ). Differences regarding the local and systemic inflammatory cytokine TNF-α reduction from baseline to day 13 post-treatment will primarily be examined through the interaction of time and treatment effects, with additional exploratory analyses performed for other days.

To assess angiographic vasospasm, serial vascular imaging studies will be evaluated. In addition to initial diagnostic imaging, patients will undergo a repeat computed tomography or catheter angiogram seven

days after admission, per our hospital’s standard protocol. Additionally, further vascular imaging will be performed if there is clinical concern per the intensive care or neurosurgical teams for clinical vasospasm or stroke. For both planned and indicated imaging sessions, each vascular imaging study will be reviewed by a trained neurointerventionalist blinded to treatment arm, who will measure and quantify the imaging as it relates to vasospasm as none, mild (< 25% stenosis), moderate (25%–50% stenosis), or severe (> 50% stenosis) narrowing of at least one major intracranial artery, as previously described [65, 66].

To evaluate the rate of chronic hydrocephalus, the primary outcome assessed will be binary (placement of ventricular shunt, versus no shunt placement).

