#### Sample size

Goal enrollment for the pilot NAVSaH trial is 50 patients, based on power calculations to detect significant differences in inflammatory cytokines, radiographic vasospasm, and chronic hydrocephalus.

Under a 2-by-2 repeated measures design consisting of two groups of patients, each measured at two time points, our goal is to compare the change across time in the taVNS group to the change across time in the Sham group. Based upon previous work from Koopman et al. [67], we assume our study will observe 1.1 standardized inflammatory cytokines mean change difference between the two groups. Using a two-sided, two-sample t-test, assuming both time points have equal variance and there is a weak correlation (i.e., 0.15) between measurement pairs, a sample size of 25 in each group achieves at least 80% power to detect a standardized difference of 1.1 in mean changes, with a significance level (alpha) of 0.05 [68].

Based upon our preliminary data, we assume this study will observe 25% and 55% severe vasospasm in the taVNS and Sham groups, respectively. Under a design with 2 repeated measurements (i.e., 2 raters), assuming a compound symmetry covariance structure with a Rho of 0.2, at a significance level (alpha) of 0.05, a sample size of 25 in each group achieves at least 80% power when the null proportion is 0.55, and the alternative proportion is 0.25 [69–71].

As previously described, LV et al. [8] studied the relationship between cytokine levels and clinical endpoints in SAH, including hydrocephalus. From their outcomes, we predict a needed enrollment of approximately 50 to detect these endpoints. From our own preliminary data, with an incidence of chronic hydrocephalus 0% in treated patients and 28.6% in control (despite grade of hemorrhage), alpha = 0.05 and power = 0.80, the projected sample size to capture that change is approximately 44 patients.

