#### Statistical methods

*Statistical methods for primary and secondary outcomes*. The primary outcome of Aim 1 is quantified continuous measures of the plasma and CSF TNF-α collected at two time points, baseline (before treatment) and day 13 after treatment. The taVNS impact on SAH inflammatory markers will be examined via a linear mixed model, where time (i.e., 0- and 13-days post-treatment), treatment (i.e., taVNS vs. Sham), and time-treatment interaction are the fixed effects, and the dependency of measurements clustered within each individual patient will be accounted for via the random effects. Group differences regarding the local and systemic inflammatory cytokines reduction from baseline to day 13 post-treatment will be examined through the interaction of time and treatment effects. Model assumptions will be inspected, and remedy will be applied if necessary. Secondary outcomes involve exploratory analyses of the remainder of the inflammatory markers collected from plasma and CSF.

The primary outcome of Aim 2 is the highest severity of vasospasm (binary, moderate/severe vs. non moderate/severe) as assessed by measurements performed by a Neurointerventionalist. A mixed effect logistic regression model will be used to examine the taVNS and Sham group difference regarding the severity of vasospasm. A generalized estimating equation (GEE) approach will be used to estimate the model parameters assuming a compound symmetry covariance structure, given there might be a possible unknown correlation between observed outcomes within the same patient. For other secondary clinical metrics related to vasospasm, to detect treatment group differences, based upon the distribution of data, independent t-tests or Wilcoxon–Mann–Whitney tests will be performed for continuous variables, and Chi-square tests or Fisher exact tests will be performed for categorical variables.

The primary outcome of Aim 3 is binary (i.e., shunt vs. non-shunt) and the secondary outcome of Aim 3 is continuous (i.e., the duration of external ventricular drainage). To detect the treatment group difference, a 2x2 contingency table and Chi-square test will be used for the binary outcome, and an independent t-test will be used for the continuous outcome.

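### The vasospasm power is calculated for severe narrowing (above 50%), but the Aim 2 primary outcome is moderate or severe narrowing (25% or more), so no power is stated for the endpoint that will be tested

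*Protocol article*

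**What the plan says.** Three sections of the protocol article bear on this.

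- **Outcomes** grades each vascular study in four levels: "none, mild (< 25% stenosis), moderate (25%–50% stenosis), or severe (> 50% stenosis) narrowing of at least one major intracranial artery".
- **Sample size** sets the planning rates: "we assume this study will observe 25% and 55% severe vasospasm in the taVNS and Sham groups, respectively". The design is described by "Under a design with 2 repeated measurements (i.e., 2 raters") and by "assuming a compound symmetry covariance structure with a Rho of 0.2, at a significance level (alpha) of 0.05", and the claim is that "a sample size of 25 in each group achieves at least 80% power when the null proportion is 0.55" and the alternative is 0.25.
- **Statistical methods** defines the tested event: "The primary outcome of Aim 2 is the highest severity of vasospasm (binary, moderate/severe vs. non moderate/severe").

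No section gives expected rates, or power, for moderate or severe vasospasm combined.

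**The concern.** By the article's own grading, the event used for planning is narrowing above 50% and the event to be tested is narrowing of 25% or more. Severe cases are a subset of the tested event, so the true rates on the tested endpoint are at least as high as the planning rates, by an amount that is not stated. The difference between arms may also change. Any prevented severe case that becomes moderate is a gain on the planned event and no change on the tested one.

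The sample size of 50 is said to rest on power calculations for three aims, and the vasospasm figure is one of them. If it describes another endpoint, a reader cannot tell what a null result on the primary vasospasm test would mean. Two cut-points on record for one primary endpoint also leave room for a choice made after the results are seen.

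**Working it through.** **Inputs.** From Sample size: 0.55 (Sham) and 0.25 (taVNS), 25 per group, M = 2 ratings, rho = 0.2, alpha = 0.05. Sidedness is not stated for this calculation; two-sided is assumed.

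**Formulas.** The variance factor for M correlated ratings is (1 + (M − 1)·rho)/M = (1 + 0.2)/2 = 0.6, so the effective n is 25/0.6 = 41.7 per group. Power with the pooled normal approximation is

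Φ{ [d·√n − 1.96·√(2·p̄(1 − p̄))] / √(p1(1 − p1) + p2(1 − p2)) },

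where d is the difference in proportions and p̄ their mean.

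**Step 1: the plan's own figure.** d = 0.30 and p̄ = 0.40.
- √(2 × 0.40 × 0.60) = 0.693
- √(0.25 × 0.75 + 0.55 × 0.45) = 0.660
- (0.30 × √41.7 − 1.96 × 0.693)/0.660 = 0.88, and Φ(0.88) = 81%

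The required number is 41 × 0.6 = 24.6, or 25 per group. The stated claim therefore reproduces. Unpooled variance gives 83.6% and the logit scale 78.2%, so the method of approximation matters little.

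**Step 2: the tested endpoint.** The moderate rates below are assumptions, because the article gives none. Severe is held at 55% vs 25%, and the two-rater factor is kept.

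| Moderate, Sham / taVNS (assumed) | Moderate or severe, Sham vs taVNS | Share of the 30-point severe reduction that reappears as moderate | Power at 25 per group |
|---|---|---|---|
| 10% / 10% | 65% vs 35% | none | 79% |
| 20% / 20% | 75% vs 45% | none | 81% |
| 30% / 30% | 85% vs 55% | none | 86% |
| 25% / 35% | 80% vs 60% | one third (10 of 30 points) | 51% |
| 25% / 45% | 80% vs 70% | two thirds (20 of 30 points) | 18% |
| 25% / 55% | 80% vs 80% | all (30 of 30 points) | no difference to detect |

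Worked example, 80% vs 60%: d = 0.20 and p̄ = 0.70; (0.20 × √41.7 − 1.96 × 0.648)/0.632 = 0.03, and Φ(0.03) = 51%.

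**Reading the table.** If moderate cases are equally common in both arms, the 30-point difference survives and power stays close to the stated figure. Power falls only as the reduction in severe cases turns into moderate cases.

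**The case against.** The strongest reply is that the mismatch may cost nothing. Severe in the Sample size section may be loose wording for moderate/severe, in which case the 81% already applies and one word needs correcting. Even if the rates are truly for severe cases, power on the tested cut could be equal or slightly higher, as the first three rows of the table show. Both points stand. They limit the size of the problem but do not remove the contradiction: the article defines severe, and nothing in it says that the planning rates mean anything else.

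A reader might go further and infer that the trial is underpowered for vasospasm. The article does not support that, because it gives no moderate rates and the low figures rest on assumed grade shifts. Nor should a figure based on one reading per patient be used to make the case. With one reading, power is about 59% for 55% vs 25% and the same 59% for 75% vs 45%, because the two pairs mirror each other (1 − 0.25 = 0.75 and 1 − 0.55 = 0.45). That shortfall comes from dropping the second rater, which is a separate question.

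A reader might also conclude that the four grades must replace the dichotomy in the primary analysis. That does not follow. Every cut ignores shifts within a category; a severe cut would ignore moderate-to-mild shifts. Enrolment began in January 2021, and Table 1 has the principal investigator reviewing clinical endpoint data quarterly, so changing the primary endpoint now risks looking data-driven. The power of an ordinal test would also depend on how the remaining patients split between none and mild, which the article does not give.

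The abstract's mention of radiographic vasospasm is ordinary shorthand and not a third definition. The pilot label does not excuse the mismatch, since the article rests enrolment on these power calculations.

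**Conclusion.** The point holds as an inconsistency in a figure the plan relies on. The power of at least 80%, reproduced as 81%, is for narrowing above 50%; the primary test is on narrowing of 25% or more; and the two sections are not reconciled anywhere in the article. Power for the tested endpoint is unstated. It lies between 79% and 86% if moderate rates of 10% to 30% are equal in both arms, and falls to 51%, 18% or nothing in the illustrative cases where one third, two thirds or all of the severe reduction becomes moderate. These figures assume severe rates of 55% and 25%, two ratings per patient with correlation 0.2, a two-sided test at 0.05 and no dropout. They show what the missing figure could be, not what it is.

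**What to change.** 1. State which cut-point the preliminary 25% and 55% describe.
2. If they describe moderate or severe vasospasm, correct the word severe in the Sample size section.
3. If they describe severe vasospasm only, take the moderate/severe proportions from the same preliminary data, then recompute and restate the power at 25 per group.
4. Use one definition in the Sample size and Statistical methods sections, and fix it before any unblinded analysis.

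An analysis of the four recorded grades may be added as supporting; it need not replace the primary analysis.

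The cost is a change of wording and one recalculation, with no new data, since all four grades are already recorded. The downside is that the restated power may be less favourable than the present claim.

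### The 80% power stated for vasospasm relies on two raters' readings per patient at correlation 0.2; the outcome as described gives one value per patient, for which 25 per group gives about 59 to 63%

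*Protocol article*

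**What the plan says.** In the protocol article, Sample size, the vasospasm calculation starts from these rates: "we assume this study will observe 25% and 55% severe vasospasm in the taVNS and Sham groups, respectively". It then sets the design: "Under a design with 2 repeated measurements (i.e., 2 raters), assuming a compound symmetry covariance structure with a Rho of 0.2". With alpha 0.05 and 25 per group it reports at least 80% power. The cytokine calculation in the same section is called two-sided; the vasospasm calculation does not say.

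Under Outcomes, "each vascular imaging study will be reviewed by a trained neurointerventionalist blinded to treatment arm". The imaging is one planned repeat study plus any further studies prompted by clinical concern.

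Under Statistical methods, the primary outcome of Aim 2 is "the highest severity of vasospasm (binary, moderate/severe vs. non moderate/severe) as assessed by measurements performed by a Neurointerventionalist". The analysis is named as a mixed-effects logistic regression, and then: "A generalized estimating equation (GEE) approach will be used to estimate the model parameters assuming a compound symmetry covariance structure". The reason given is a possible correlation among a patient's outcomes. The text does not say whether those outcomes are raters, scans or something else. No second rater is mentioned outside Sample size.

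**The concern.** A per-patient maximum, dichotomised, is one record. The power statement assumes two records per patient that are only weakly correlated, and it credits the trial with the resulting gain in information. If the analysis has one record per patient, that gain does not exist. A true 30-point difference would then be missed about 40% of the time, not 20%, and a null vasospasm result would be over-read. Vasospasm is one of the primary endpoints, and the enrolment goal of 50 is justified partly by this calculation.

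The analysis sentence leaves the same question open. A mixed-effects logistic model (conditional) and a GEE (marginal) are different models, and both need repeated records that the outcome definition does not supply. If the repeats were scans, patients with more clinically triggered imaging would contribute more records, and the analysed quantity would no longer be the worst grade.

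**Working it through.** **Inputs (Sample size).** p1 = 0.55, p2 = 0.25, n = 25 per group, m = 2 ratings, rho = 0.2, alpha = 0.05. Two-sided testing is my assumption. No dropout is applied because none is stated for this calculation.

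**Formulas.**
- Effective patients per group: n_eff = n × m / (1 + (m − 1) × rho).
- Pooled-z power: Φ[(0.30 − 1.96 × √(2 × 0.40 × 0.60 / n_eff)) / √((0.55 × 0.45 + 0.25 × 0.75) / n_eff)]. Here 2 × 0.40 × 0.60 = 0.48 and 0.2475 + 0.1875 = 0.435.

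**Step 1: the plan's figure.** n_eff = 25 × 2 / 1.2 = 41.67. Power = Φ[(0.30 − 1.96 × 0.1073) / 0.1022] = Φ(0.877) = 81.0%. The unpooled version gives 83.5%. The n for 80% with one record is 40.66 per group; multiplied by 1.2 / 2 = 0.6 this is 24.4, which rounds up to 25. The stated sample size is therefore what the two-rater assumption yields.

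**Step 2: one record per patient.** n_eff = 25. Power = Φ[(0.30 − 1.96 × 0.1386) / 0.1319] = Φ(0.215) = 58.5%.

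| Test, 25 per group, one record | Power |
|---|---|
| Pooled z, two-sided | 58.5% |
| Unpooled z, two-sided | 62.3% |
| Pearson chi-square, exact enumeration | 62.6% |
| Wald test on the log-odds scale, two-sided | 56.4% |
| Pooled z, one-sided | 70.8% |

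The log-odds Wald test gives 78.2% under the plan's own two-rater inputs, so it runs a little lower throughout. For 80% power, two-sided, with one record, 41 per group (82 in total) are needed without continuity correction.

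**Step 3: two raters kept, correlation varied.** The document gives no inter-rater agreement, so the values other than 0.2 are illustrative (pooled z, two-sided).

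| rho | n_eff | Power |
|---|---|---|
| 0.2 | 41.67 | 81.0% |
| 0.5 | 33.33 | 71.5% |
| 0.7 | 29.41 | 65.8% |
| 0.8 | 27.78 | 63.2% |
| 0.9 | 26.32 | 60.8% |

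The highest rho that keeps 80% solves 50 / (1 + rho) = 40.66, so rho = 0.23. With the unpooled requirement of 37.94 it is 0.32.

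**Step 4: what rho 0.2 means for two readers.** With equal marginal rates, the probability that two binary readings agree is p² + (1 − p)² + 2 × rho × p × (1 − p). At p = 0.55: 0.3025 + 0.2025 + 0.099 = 0.604. At p = 0.25: 0.0625 + 0.5625 + 0.075 = 0.70. The assumption is thus that two readers of the same patient's images agree in about 60% of sham and 70% of taVNS patients.

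**Step 5: threshold.** Outcomes grades moderate as 25 to 50% stenosis and severe as above 50%. The assumed rates are for severe alone, whereas the Aim 2 endpoint counts moderate and severe together. The rates, and hence the power, for the analysed endpoint cannot be derived from the document.

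**The case against.** The best defence is that two records per patient may really be intended. Sample size and Statistical methods both specify compound symmetry, and the latter gives within-patient correlation as the reason, which presupposes more than one record. The singular neurointerventionalist may describe the reader's specialty and not the number of readers. Each of two raters could supply a worst grade, and reader logistics are often left to a full protocol. This stands as far as it goes: a two-record reading is possible. The 59 to 63% figure, and any claim that a random intercept cannot be identified, are therefore conditional on one record per patient.

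The two-record reading saves the stated power only if the correlation is near 0.2 or lower in a two-sided test. A one-sided test would be more forgiving: it needs 31.91 per group with one record, so 80% would survive up to rho = 50 / 31.91 − 1 = 0.57. The document does not say that this test is one-sided.

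A reader might infer that the power was miscalculated. It was not; the stated figure follows from its stated inputs. A reader might also infer that rho 0.2 is shown to be wrong. The document has no agreement data, so it can only be called an unsupported assumption with the consequence shown in Step 4. Finally, the pilot label softens the consequences, but the Trial design section states a superiority aim for vasospasm and the power claim is made outright.

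**Conclusion.** The concern holds as a mismatch between the power inputs and the endpoint as described. The stated 80% is reached only by counting two readings per patient at rho 0.2. With the single worst grade that Outcomes and Statistical methods describe, power for 55% versus 25% is about 59 to 63% two-sided and about 71% one-sided. No single-record version tested reaches 80%.

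This rests on three assumptions: one record per patient, no dropout, and the 55% and 25% rates applying to the endpoint. The last is doubtful because the rates are given for severe vasospasm. A reader might therefore take about 60% as the trial's actual power for moderate or severe vasospasm; the document does not support that, since it gives no rates for that threshold.

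**What to change.** 1. State how many raters read each study and how many records per patient enter the primary vasospasm analysis, in the same terms in Outcomes, Sample size and Statistical methods.
2. If there is one worst post-baseline grade per patient, remove the two-rater, rho 0.2 gain from Sample size. State that 25 per group gives about 60% power for a 55% versus 25% difference, and say whether the test is two-sided.
3. In that case, replace the mixed-model and GEE text with ordinary logistic regression on one record per patient, reported with a risk difference and 95% CI. Reduce any second read to one adjudicated grade before analysis.
4. State which threshold the 25% and 55% rates refer to, and recompute the power with rates for the threshold that is analysed. The figure in item 2 should not be attached to the moderate-or-severe endpoint until this is done.

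The cost is a less favourable stated power and a small analysis amendment, which would go through the IRB review that the protocol requires for amendments. No extra patients or readers are needed.

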#### Recruitment

Members of the Neurosurgical team and Intensive Care team identify potential candidates for the NAVSaH trial and notify the research team who conducts formal screening to determine candidacy. Recruitment outside of the hospital, or prior to admission, is not performed.

#### Assignment of interventions: Allocation

*Sequence generation*. Participants are randomized 1:1 to receive treatment with taVNS or Sham stimulation. Randomization is via a simple randomization via computer generated random generated numbers, with next-number obscured until after consent is completed and time of patient enrollment into the study.

*Concealment mechanism*. The computer-generated randomization sequence is concealed, and the treatment group allocation via random number generation occurs only after the patient has been consented and enrolled in the trial. Following assignment of treatment group, treatment arm remains concealed to the patient, medical team, and outcomes assessors.

*Implementation*. Treatment group allocation is via a simple randomization via computer generated random number assignment (0 vs 1). Patients are enrolled prior to randomization by a member of the research team who goes through the informed consent process with the patient, or their legally authorized representative when appropriate. A single investigator is responsible for entering the patient into the computer system to ascertain the assigned treatment arm.

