*Methods for additional analyses (e*.*g*. *subgroup analyses)*. To evaluate for effect of grade of hemorrhage (high grade with a Hunt and Hess Score ≥3, versus low grade), the interaction between assigned treatment and the subgroup factor in a linear model will be tested (significance level of P<0.017). The model will include a main effect for treatment, subgroup factor, and an interaction between subgroup and treatment. Secondary outcomes will also be assessed in similar models.

*Methods in analysis to handle protocol non-adherence and any statistical methods to handle missing data*. High levels of missing data for the outcomes of interest are not expected because these are readily available, documented in medical records as part of the standard of medical care for SAH, and are ascertained during the patient’s primary hospital admission. Should there be high rates of participant attrition in the trial, baseline characteristics and available information on the hospital course will be reviewed and compared to participants who do not withdraw from participation to assess for any differences in those who withdraw and those who do not.

*Plans to give access to the full protocol*, *participant level-data and statistical code*. A dataset with group-level, de-identified clinical data and participant-level de-identified laboratory data in accordance with the Health Insurance Portability and Accountability Act (HIPAA), as well as statistical code used for analyses and will be made available upon reasonable request. The team will comply with the clinical trial information dissemination expectations of the NIH policy and FDA/DHHS Final Rule to register and submit summary results at ClinicalTrials.gov. Consistent with the terms and conditions of NIH funding, we will ensure the submission and updating of registration and results information for this clinical trial in the timeframes established by the Final Rule.

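### Fifty patients under simple randomisation, and no hemorrhage grade in the primary analyses: the tests are valid, but prespecified adjustment would guard against a 1-in-6 imbalance at little cost

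*Protocol article*

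**What the plan says.** Protocol article, Sample size: "Goal enrollment for the pilot NAVSaH trial is 50 patients", planned as 25 per group.

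Assignment of interventions: Allocation: "Participants are randomized 1:1 to receive treatment with taVNS or Sham stimulation". The method is "Randomization is via a simple randomization via computer generated random generated numbers", implemented as a 0/1 draw. No block or stratum is named.

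Statistical methods sets out the three primary analyses:
- **TNF-α:** a mixed model whose fixed effects are listed as time, treatment and their interaction.
- **Vasospasm** (moderate/severe or not): a logistic model, fitted by GEE, for the group difference. No covariate is named.
- **Shunt:** "a 2x2 contingency table and Chi-square test will be used for the binary outcome".

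Grade appears under the additional analyses, where the subgroup factor is "grade of hemorrhage (high grade with a Hunt and Hess Score ≥3, versus low grade". That model has treatment, grade and their interaction. Grade is therefore a defined and available baseline variable, but it is used outside the primary tests.

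**The concern.** With about 25 patients per arm and nothing in the allocation to balance severity, the arms can differ noticeably in hemorrhage grade. If grade predicts vasospasm, shunting or the change in TNF-α, an unadjusted comparison in such a trial carries part of that difference into the estimated treatment effect. The data needed to allow for it are already collected. If adjustment is not prespecified, the only alternative is to decide on it after the imbalance has been seen, and that decision would be open to the charge of being data-driven.

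**Working it through.** **Inputs from the protocol article.** N = 50, 25 per arm, simple 1:1 randomisation. TNF-α: difference 1.1, pair correlation 0.15, two-sided alpha 0.05. Vasospasm: 25% vs 55%, two raters, rho 0.2. Shunt: 0% vs 28.6%.

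**Assumed, because the document gives neither.** The high-grade share (30–60%) and the prognostic strength of grade.

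**1. The plan's own figures.**
- TNF-α: SD of change = √(2(1 − 0.15)) = 1.304, so d = 1.1/1.304 = 0.844. A two-sample t-test with 25 per arm has 83.2% power. This reads 1.1 in units of the single-measurement SD.
- Vasospasm: effective n = 25 × 2/(1 + 0.2) = 41.7 per arm, power 81.0%.
- Shunt: 23 per arm, 46 in total, against the stated figure of about 44.

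All three reproduce closely.

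**2. Arm sizes under simple randomisation.** From Binomial(50, 0.5), exactly 25:25 occurs in 11% of trials, 20:30 or worse in 20%, and 18:32 or worse in 6.5%. This costs little: TNF-α power is 83.2% at 25:25, 81.7% at 20:30 and 80.1% at 18:32.

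**3. Grade imbalance (simulation).** A between-arm difference in high-grade share of at least 20 points arises in 13%, 16%, 17% and 16% of trials for a high-grade share of 30%, 40%, 50% and 60%.

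**4. False-positive rate of the binary tests under a true null.** 20,000 simulated trials, half the patients high grade; assumed risks (high/low grade) of 45%/12% for shunt and 57%/23% for vasospasm, one binary result per patient.

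| | All trials: unadjusted | All trials: stratified | Imbalance ≥20 points: unadjusted | Imbalance ≥20 points: stratified |
|---|---|---|---|---|
| Shunt | 5.2% | 5.0% | 9.0% | 4.8% |
| Vasospasm | 5.4% | 4.8% | 8.9% | 4.3% |

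The last two columns rest on about 20,000 × 0.17 = 3,400 trials, so a 9% rate has a simulation standard error of √(0.09 × 0.91/3,400) = 0.5 points.

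**5. One fixed imbalance.** Take 10/25 against 15/25 high grade and no treatment effect.
- Risks 30% (low) and 60% (high): expected rates are 0.4 × 60 + 0.6 × 30 = 42% and 0.6 × 60 + 0.4 × 30 = 48%, a spurious 6 points. The chi-square test rejects 7.6% of the time, the stratified test 4.7%.
- Risks 20% and 70%: 40% and 50%, a spurious 10 points. Rejection 9.4% against 4.5%.

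In the first case false findings favour the lower-severity arm 6.7% of the time and the other arm 0.8%. Without a grade effect they run at about 3.2% each way.

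**6. What adjustment gains or costs.**
- TNF-α power, unadjusted vs adjusted, when grade explains 0%, 10%, 20% and 30% of the variance in change: 82% vs 81%, 83% vs 86%, 82% vs 88%, 82% vs 93%. At exactly 25:25 the loss from one degree of freedom is 83.21% to 83.18%.
- Vasospasm power with one binary result per patient: 60% vs 63% if grade is strongly prognostic, 60% vs 58% if it is not.
- Shunt at 0% vs 28.6%: unadjusted 93.4%, stratified 93.7%.

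**7. The form of adjustment matters.**
- TNF-α: with two complete measurements per patient, the time-by-treatment term is the difference in mean change. A grade main effect shifts both time points equally and cancels from the change, so the estimate does not move. A grade-by-time term is needed.
- Shunt: with a true treated rate of 0% there are no treated events, so the treatment log-odds ratio has no finite maximum-likelihood estimate. Ordinary logistic regression with grade separated in 100% of simulated trials.

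**The case against.** The strongest reply is that nothing here is an error. Simple randomisation followed by unadjusted tests is a valid and common design, and this is a pilot. The excess false positives appear only after conditioning on an imbalance that most trials will not have, and the spurious 6 points is about a fifth of the differences the plan is powered for (30 points for vasospasm, 28.6 for shunt). All of that stands, and it limits the point to conditional error and precision.

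The prognostic strength of grade is also assumed. The Sample size section remarks that the preliminary hydrocephalus difference arose regardless of grade. A reader might take that remark, or the subgroup model, as proof that grade is prognostic. Neither shows it: the remark gives no figures, and a test for effect modification says nothing about prognosis.

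It can also be said that covariates belong in a separate analysis plan, and that the subgroup model already contains grade. The first defence is fair for the vasospasm model, whose terms are not listed. It is weak for TNF-α and shunt, where the fixed effects and the test are spelled out. The second does not help, because the subgroup model is not the primary test.

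**Conclusion.** The point holds as a cheap improvement. About 1 trial in 6 will show a grade difference of 20 points or more. In those trials, if grade is prognostic to the degree assumed, the unadjusted binary tests reject a true null about 8–9% of the time against about 5% with stratification. For TNF-α the gain is power, from 82% to 88% if grade explains 20% of the variance in change.

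Three stronger readings are tempting and are not supported:
- **That the primary tests are biased or invalid.** Over all randomisations they stay near 5%.
- **That a large imbalance is likely.** It is a minority outcome at 13–17%.
- **That adjustment removes the imbalance at no cost.** It corrects the comparison for one factor, leaves other factors and uneven arm sizes alone, and has a small price.

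The high-grade share and the strength of the grade effect are assumptions throughout. The allocation figures in step 2 do not depend on them.

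**What to change.** By a dated amendment, made before anyone deciding on it has seen results by arm, prespecify Hunt and Hess grade (3 or more vs lower) in the primary analyses:
- **TNF-α:** add grade and grade-by-time to the mixed model, or analyse day 13 by ANCOVA with baseline and grade. A grade main effect alone is not enough.
- **Vasospasm:** add grade to the logistic/GEE model and name the grade-adjusted odds ratio as the estimand, since it differs from the unadjusted one.
- **Shunt:** replace the plain chi-square by a Cochran-Mantel-Haenszel test stratified by grade, or by an exact or penalised model. Do not use ordinary logistic regression.

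Keep the unadjusted results as sensitivity analyses. N stays at 50, allocation is unchanged and no new data are needed.

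The statistical cost is one or two degrees of freedom for TNF-α and about 2 points of vasospasm power if grade is not prognostic. The procedural cost is real as well: enrolment began in January 2021, and Table 1 has the principal investigator reviewing clinical and laboratory endpoints quarterly. The amendment should therefore record what had been seen, and by whom, when it was made.
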